### Inclusion/exclusion criteria

At this stage of validation, the screener will be conducted in the English language only, thus proficiency in reading the English language is required. Participants under the age of 14 are excluded from the study – separate validation studies are indicated for younger age groups due to differences in comparison measures, linguistic ability and potential impact on item comprehension. Also excluded are those with no reliable access to the internet. Otherwise, no further demographic or exclusion criteria will be set. Participants with a current diagnosis of an eating disorder as well as those with no current or former diagnosis are equally welcome to participate: these two groups (clinical and non-clinical) will be defined and compared post testing using EDE-Q cut-off scores.

### Overall study design

This study will use a cross-sectional survey research design with follow up on a sub-sample to examine the 6-item IOI-S for statistical reliability and validity. Participants will be given access to a baseline survey package delivered on the secure web survey platform REDCap. Approximately half the participants will be randomly selected to participate in a follow-up re-test involving completion of the IOI-S alone a second time 2 weeks post initial testing, to account for potential drop-out/uptake refusal. 30% is needed for sufficient test-retest reliability.

### Measures

Four questionnaires make up the baseline survey package: The EDE-Q, the SCOFF Questionnaire, the IOI-S and either the Marlowe-Crowne Social Desirability Scale (MC-SDS) (adults) or Children’s Social Desirability Short Scale (CSD-S) (adolescents), described in full below. The four existing surveys against which the IOI-S will be measured were chosen as the relevant diagnostic tools most frequently used in clinical settings and research trials. These will be presented in randomised order to the participants.

### Baseline package

#### InsideOut institute screener (IOI-S) (InsideOut Institute for Eating Disorders, [44])

The six items of the new scale are displayed in Table 1. Item development followed review of the scientific literature for existing instruments screening and assessing eating disorder symptomatology, lived experience and clinical and research expert consultation. Instruments reviewed included the EDE-Q, the Eating Disorders Inventory (Garner et al., [46]), the SCOFF questionnaire, the ESP, and the Eating Attitudes Test (EAT; Garner et al., [47]), from which researchers developed an initial pool of 10 questions covering six facets of eating pathology: an individual’s relationship with food, body, the extent to which body weight and shape determines self-worth, loss of control over eating, binge eating and compensatory behaviour. This was further narrowed by an expert consultation team to six relevant items to evaluate eating pathology and eating disorder risk in a non-clinical population. The IOI-S is rated on a 5-point Likert scale, where 1 is “never” and 5 is “all the time”; except for Question 1, where 1 is “worry and stress free” and 5 is “full of worry and stress”. Responses are summed to yield a score between 6 and 30 points total, where 6 points is the lowest degree of risk and 30 points the highest degree of risk. Those deemed to be of moderate to high risk are directed to InsideOut’s database of trained professionals with expertise in eating disorders.

**Table 1 Tab1:** 6-item insideout institute screener

Item	1	2	3	4	5
1. How is your relationship with food?	Worry and stress-free	A bit problematic	Moderately problematic	Very problematic	Full of worry and stress
2. Does your weight, body or shape make you feel bad about yourself?	Never	A little bit	Sometimes	Quite a bit	All the time
3. Do you feel like food, weight or your body shape dominates your life?	Never	A little bit	Sometimes	Quite a bit	All the time
4. Do you feel anxious or distressed when you are not in control of your food?	Never	A little bit	Sometimes	Quite a bit	All the time
5. Do you ever feel like you will not be able to stop eating or have lost control around food?	Never	A little bit	Sometimes	Quite a bit	All the time
6. When you think you have eaten too much, do you do anything to make up for it?	Never	A little bit	Sometimes	Quite a bit	All the time

#### Eating disorder examination questionnaire (EDE-Q) (Fairburn & Beglin, [20])

The EDE-Q is a 28-item self-report version of the EDE structured clinical interview which is regarded as the ‘gold-standard’ diagnostic tool in eating disorders and has been validated in multiple trials [48]. Traditionally paper-based, it has been psychometrically validated for online delivery [49]. It includes additional measures of weight, height, and missed menstrual periods, the latter of which will be excluded from our study due to the DSM-5 removal of and consequent diagnostic irrelevance of missed menstruation in ED. It is comprised of a global score and four subscales: Restraint, Eating Concern, Weight Concern, and Shape Concern, and employs a 7-point forced-choice severity rating where 0 points is the lowest severity and 6 points is the highest severity.

#### SCOFF (sick, control, one stone, fat, food) questionnaire (Morgan et al., [21])

The SCOFF questionnaire is a short 5-item forced choice (true/false) screening tool designed to assess eating disorder symptomatology. A threshold of > 2 positive answers indicates a ‘likely case’ of AN or BN. It has shown good internal consistency and concurrent validity with the EDE-Q [50]. The SCOFF is included due to the frequency with which it has been employed in clinical and research settings.

#### Eating Disorder Examination Questionnaire 8 (EDE-Q8) (Kliem et al., [28]

The EDE-Q8 is an 8-item short form of the longer EDE-Q, designed as an abbreviated outcome measure that retains the original factor structure. It is highly correlated with the EDE-Q and demonstrates strong internal consistency, concurrent and convergent validity. Items are drawn directly from and are identical to respective items in the EDE-Q and will be extracted for independent analysis in this instance.

#### Marlowe-Crowne Social Desirability Scale (MC-SDS) (Crowne & Marlowe, [51])

The MC-SDS is a well-validated 33-item self-report questionnaire measuring social desirability in adults by evaluating concern with social approval. Items are rated true/false and balanced for positive and negative wording. It is frequently used as a measure of discriminant validity in instrument design [52] and has shown good divergent validity with measures of psychopathology (anxiety, depression) related to eating disorders [53]. The MC-SDS is not validated for use in children: thus, an adapted Children’s Social Desirability Scale (CSD-S) will apply for those participants aged under 18.

#### Children’s Social Desirability Short Scale (CSD-S) (Baxter et al, [54])

The CSD-S is an abbreviated 14-item version of the gold-standard 48-item Children’s Social Desirability scale developed by Crandall, Crandall and Katovsky in [55]. The original scale was modelled on the MC-SDS for adults and is validated for use in a child/adolescent population [54]. It will be assigned to our 14 to 17-year-old participants. The scale uses binary response (yes/no) and is regularly used for methodological validity to detect confounding from social desirability bias. The CSD-S has demonstrated adequate internal consistency and test-retest reliability and good external validity [56].

### Follow-up package

#### InsideOut institute screener (IOI-S) (InsideOut Institute for Eating Disorders, [44])

Follow-up involves completion of the 6-item IOI-S only.

### Sample size calculation

Estimated sample size is based on 2.5–3 times the minimum sample size required for power as the outcome measure (statistical validity) is incrementally increased with participant numbers. Therefore, we anticipate a total sample size of approximately 250 participants.

Approximately 30% of participants in each of the clinical and non-clinical groups (defined post T1 on EDE-Q cut-off score) will need to engage in the second task for sufficient validity. Estimated minimum sample size is based on the following analysis: in each group 10 participants are required for a power of 0.80 to detect an intraclass correlation coefficient of 0.70; 80 participants are required for sufficient power to detect a Spearman’s correlation of 0.40 or higher; 80 participants are required for good power to detect an Area Under Curve of 0.70, and at least 50 participants for a correlation coefficient of r +/− 0.70 for convergent and discriminant validity. All power analyses were conducted using PASS version 15 software [57].

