### Data analyses

#### Reliability

Reliability is an important feature of survey efficacy indicating the overall replicability and internal stability of a measure [58]. Measure reliability of the IOI-S will be examined on two parameters: internal consistency and test-retest reliability. The internal consistency, that is, the degree to which the six items on the scale measure the same underlying dimension, will be calculated using a standardized Cronbach’s alpha score, with a minimum acceptable threshold of > .80 [59]. An exploratory factor analysis will be performed on the IOI-S items using principal axis factoring and Promax oblique rotation to examine factor loading, with an item-total correlation threshold of >.40 [60, 61]. Correlations between successive iterations of the test (test-retest reliability) will be reviewed using a 2-way mixed effects model Intraclass correlation coefficient with absolute agreement and a minimum acceptable threshold of > 0.70 [62].

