#### Criterion validity

The degree to which the results on the IOI-S are able to predict an outcome on established measures of eating disorder symptomatology (concurrent validity) [63] will be assessed as concordance between the IOI-S, the EDE-Q, and the SCOFF using a Spearman’s product moment correlation. Following, an Area Under Curve (AUC) analysis of Receiver Operating Characteristic (ROC) curve will be performed as analysis of IOI-S sensitivity and specificity threshold where a high sensitivity indicates accurate identification of true positive cases and high specificity indicates accurate identification of true negative cases [64]. Area Under Curve dictates the probability of identifying true positives or negatives by chance, where a value of 0.50 would suggest the measure is no more effective than guessing [65]. AUC threshold will be set at > 0.70 with a 95% confidence interval.

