#### Construct validity

Convergent validity, or the degree to which the IOI-S correlates with eating disorder constructs and variables on both the EDE-Q and the SCOFF [66] will be measured with a correlation coefficient threshold set at *r >* 0.70. A correlation coefficient will also be determined for discriminant validity between the IOI-S and MC-SDS/CSD-S. A correlation coefficient of +/− 0.70 indicates a strong linear relationship between two variables [67].

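### The power of 0.80 claimed for 10 participants per group fits a test against an ICC of about zero, not against the acceptance mark of ICC > 0.70

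*Protocol article*

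**What the plan says.** The protocol article, Sample size calculation, states that "in each group 10 participants are required for a power of 0.80 to detect an intraclass correlation coefficient of 0.70". It adds that "80 participants are required for good power to detect an Area Under Curve of 0.70", and asks for "at least 50 participants for a correlation coefficient of r +/− 0.70 for convergent and discriminant validity". Only the ICC line carries a numerical power. No null value, alpha or sidedness is given for any of them.

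The acceptance marks stand under Data analyses and use the same number:

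- Reliability: the test-retest ICC is a two-way mixed model with "absolute agreement and a minimum acceptable threshold of > 0.70".
- Criterion validity: "AUC threshold will be set at > 0.70 with a 95% confidence interval". The same section explains that "a value of 0.50 would suggest the measure is no more effective than guessing", but does not name 0.50 as the null of the power analysis.
- Construct validity: the convergent correlation "will be measured with a correlation coefficient threshold set at" r > 0.70.

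The planned total is about 250. On the retest, Overall study design says: "Approximately half the participants will be randomly selected to participate in a follow-up re-test". About 30% of each group must complete it.

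**The concern.** A power statement answers one question: how likely is the study to reject a given null if a given alternative is true? Here the alternative (0.70) equals the acceptance mark (0.70). If the null were also 0.70, power would equal alpha. So the stated 0.80 must refer to a null well below 0.70, and rejecting such a null does not show that the ICC exceeds 0.70.

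At stake is the study's main claim, that the screener is reliable and valid. A reader of the sample size section would think that test-retest reliability is secured with 10 people per group. Nothing in that calculation bears on the criterion by which reliability will be judged.

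**Working it through.** **Inputs.** From the article: ICC 0.70, n = 10 per group, power 0.80; k = 2 measurements (baseline and one retest); acceptance marks of 0.70; N about 250; about half invited to retest; 30% of each group needed. Assumed: alpha 0.05, one- and two-sided both tried, and equal clinical and non-clinical groups of 125. Planned retests are then 0.30 × 125 = 37.5, taken as 37 per group, and 0.30 × 250 = 75 pooled.

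**1. Reproducing n = 10.** Let θ(ρ) = 1 + kρ/(1 − ρ). The observed F ratio divided by θ(ρ) follows F(n − 1, n), or F(n − 1, n − 1) with two-way degrees of freedom. Power = P(F > F_crit × θ(ρ0)/θ(0.70)).

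θ(0) = 1 and θ(0.70) = 1 + 1.4/0.3 = 5.667. For n = 10, one-sided 0.05, F_crit = 3.020 and power = P(F > 3.020/5.667) = P(F > 0.533) = 0.82. With two-way degrees of freedom, F_crit = 3.179 and power is 0.80. Two-sided, power is 0.72 and 0.69.

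Other nulls (one-sided, first form):

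| Null ICC | Power at n = 10, true ICC 0.70 |
|---|---|
| 0 | 0.82 |
| 0.1 | 0.73 |
| 0.3 | 0.50 |
| 0.5 | 0.24 |
| 0.7 | 0.05 |

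The printed figure fits a null of about zero.

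**2. Chance of meeting the acceptance mark.**

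- Point-estimate rule: P(estimate > 0.70) = P(F > 5.667/θ(ρ)).
- Lower-limit rule (two-sided 95% interval): P(F > F_0.975 × 5.667/θ(ρ)).

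θ(0.60) = 4 and θ(0.80) = 9. Example at n = 75, ρ = 0.80: F_0.975 = 1.580, and 1.580 × 5.667/9 = 0.995, giving 0.51.

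| True ICC | Estimate > 0.70, n = 37 | n = 75 | Lower limit > 0.70, n = 37 | n = 75 |
|---|---|---|---|---|
| 0.60 | 0.15 | 0.07 | – | – |
| 0.70 | 0.50 | 0.50 | 0.025 | 0.025 |
| 0.80 | 0.92 | 0.98 | 0.28 | 0.51 |
| 0.85 | 0.99 | >0.99 | 0.64 | 0.91 |

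The row for 0.70 is the same at n = 10. More participants do not change it.

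**3. AUC.** With Hanley-McNeil standard errors, AUC 0.70 against 0.50 at 40/40 gives (0.20 − 1.96 × 0.0650)/0.0585 = 1.24, power 0.89 two-sided. That is consistent with good power but does not prove a null of 0.50. Against 0.70 with true AUC 0.80 at 125/125, the standard error is 0.0280 and 0.10/0.0280 − 1.96 = 1.61, probability about 0.95. It is 0.90 if the standard error under 0.70 is used for the limit.

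**4. Convergent r.** Fisher z, r = 0.70 against 0 at n = 50: power above 0.99. A null of zero is therefore not confirmed; 80% power at n = 50 would match a null of about 0.41 to 0.46. Against 0.70 with true r 0.80: (1.0986 − 0.8673) × √(n − 3) − 1.96 gives −0.37 at n = 50 (0.35) and 1.68 at n = 250 (0.95).

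**The case against.** Four points can be made for the plan.

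1. *A minimum acceptable threshold is a benchmark for reading an estimate, and any benchmark is met about half the time when the truth lies exactly on it.* This stands. The 50% figure shows no shortage of participants. It shows that a calculation at 0.70 says nothing about passing at 0.70. Nor does the article say that 0.70 is the value it expects.

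2. *The actual sample is far larger than 10 per group.* This also stands. About 37 per group or 75 pooled will be retested, and under a point-estimate rule a true ICC of 0.80 then passes 92% and 98% of the time. The total of 250 is not driven by the ICC line: 250/3 = 83 and 250/2.5 = 100, close to the minima of 80. Pass rates or intervals worked at n = 10 would not describe this study.

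3. *The lower-limit rule is not in the plan.* For ICC and r it is not stated. For the AUC the wording can be read either way. The 2.5% and 0.51 figures depend on that reading.

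4. *Nulls and decision rules may be left to the full protocol or analysis plan.* In general, yes. But the article itself prints the sample size, the power and the threshold, and these do not fit together.

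A reader might go further and infer that all three criteria were powered at 80% against zero or chance, and that all three really have 50%. The article does not support that. The figure 0.80 is given for the ICC alone, the AUC has only a verbal description, and r has no power at all. The Spearman 0.40 line and discriminant validity, where a high correlation is not the aim, are outside the point.

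**Conclusion.** The point holds for the ICC sentence. Its power of 0.80 belongs to a test against an ICC of about zero, a hypothesis that the analysis section does not use. This rests on inferred settings (null about zero, one-sided alpha 0.05). The mismatch itself needs only that the null lies below 0.70, which must be so.

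The practical size depends on the rule. If the lower 95% limit must exceed 0.70, test-retest reliability is the weak criterion: about 0.28 per group and 0.51 pooled for a true ICC of 0.80, rising to 0.91 pooled for 0.85. If the point estimate suffices, the chance at a true 0.80 is high, but a true 0.60 passes wrongly 15% of the time at 37 per group and 7% at 75 pooled.

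The AUC and convergent r items share the flaw of planning at the pass mark, but their nulls cannot be confirmed. At N = 250 both look adequate for a true value of 0.80, the AUC under an equal clinical split. It would be too strong to conclude that the retest cannot tell acceptable from unacceptable reliability: an observed ICC of 0.80 at 75 pairs has a 95% interval of about 0.70 to 0.87.

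**What to change.** - Remove the statement that 10 participants per group suffice for the ICC.
- For ICC, AUC and convergent r, state whether the estimate or the lower 95% limit must exceed 0.70, preferably the lower limit.
- Restate power against 0.70 with a planning value above it, and print the null, alpha and sidedness. For a true value of 0.80 under the lower-limit rule: ICC about 0.51 at 75 pooled pairs, AUC about 0.95 at 125/125 (0.90 by the more cautious formula), r about 0.95 at n = 250. The AUC figure assumes an equal clinical split.

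These changes cost some rewriting and a less favourable figure for the ICC. Enrolment does not change.

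Optional, at low cost: invite all participants to the six-item online retest instead of a random half. Reaching 75 of 125 invited already needs 75/125 = 60% uptake. That is the uptake required, not a forecast. If 60% were achieved among all 250, there would be 0.60 × 250 = 150 pairs. With a true ICC of 0.80, the pooled chance under the lower-limit rule would rise from 0.51 to about 0.80, and the per-group chance (75 pairs each) from 0.28 to about 0.51. The cost is about 125 more invitations.

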### Data analyses

#### Reliability

Reliability is an important feature of survey efficacy indicating the overall replicability and internal stability of a measure [58]. Measure reliability of the IOI-S will be examined on two parameters: internal consistency and test-retest reliability. The internal consistency, that is, the degree to which the six items on the scale measure the same underlying dimension, will be calculated using a standardized Cronbach’s alpha score, with a minimum acceptable threshold of > .80 [59]. An exploratory factor analysis will be performed on the IOI-S items using principal axis factoring and Promax oblique rotation to examine factor loading, with an item-total correlation threshold of >.40 [60, 61]. Correlations between successive iterations of the test (test-retest reliability) will be reviewed using a 2-way mixed effects model Intraclass correlation coefficient with absolute agreement and a minimum acceptable threshold of > 0.70 [62].

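### Internal consistency is judged by standardized alpha although the IOI-S is scored as a raw sum, and alpha above .80 cannot show that the six items form one dimension (minor)

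*Protocol article*

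**What the plan says.** All of this is in the protocol article.

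- **Scoring (Baseline package, IOI-S).** "The IOI-S is rated on a 5-point Likert scale, where 1 is “never” and 5 is “all the time"; Question 1 has other anchors but the same 1-to-5 range. "Responses are summed to yield a score between 6 and 30 points total".
- **Internal consistency (Data analyses, Reliability).** It is glossed as "the degree to which the six items on the scale measure the same underlying dimension" and "will be calculated using a standardized Cronbach’s alpha score, with a minimum acceptable threshold of > .80".
- **Structure (same section, next sentence).** "An exploratory factor analysis will be performed on the IOI-S items using principal axis factoring and Promax oblique rotation to examine factor loading". The only numeric mark attached to this analysis is that each item should correlate above .40 with the total.
- **Content (Baseline package, IOI-S).** The initial ten-question pool is described as "covering six facets of eating pathology", later cut to six items.

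**The concern.** Two mismatches sit in one sentence of the Reliability section.

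First, standardized alpha is the reliability coefficient of a sum of z-scored items. Respondents receive the sum of the raw responses, and no z-scored total is described anywhere. The pass mark is thus set on a coefficient for a score that is not used.

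Second, the gloss treats alpha as a measure of how far the items share one dimension. For a fixed number of items, standardized alpha depends only on the mean inter-item correlation. It cannot tell one factor from two correlated ones. The item pool was built to span several facets, so more than one factor is plausible.

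At stake is how one of the two reliability results is reported: whether the 6-to-30 score itself meets the .80 mark, and whether meeting it is described as evidence of a single dimension.

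**Working it through.** The .80 mark is a cited threshold, so there is no derived figure to reproduce. From the document: k = 6 items, each scored 1 to 5 and summed; threshold .80; item-total mark .40. Item SDs and inter-item correlations are not given, so those below are assumptions.

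**What the mark requires.** Standardized alpha = k·r̄ / (1 + (k − 1)·r̄), where r̄ is the mean inter-item correlation. Setting it to .80 with k = 6 gives r̄ = .80 / (6 − 5 × .80) = .40. The criterion says only that the mean correlation exceeds .40.

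**Standardized against raw alpha.** Raw alpha = k/(k − 1) × (1 − sum of item variances / variance of the sum). Take r̄ = .42 throughout, so standardized alpha = 2.52 / 3.10 = .813.

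| Assumed item SDs (items 1–6) | Assumed correlations | Sum of item variances | Variance of sum | Raw alpha |
|---|---|---|---|---|
| all equal to 1 | all .42 | 6.00 | 18.60 | .813 |
| 1.1, 1.4, 1.4, 1.3, 1.2, 0.8 | all .42 | 8.90 | 26.93 | .803 |
| 1.0, 1.5, 1.5, 1.4, 1.2, 0.6 | all .42 | 9.26 | 27.14 | .791 |
| 1.0, 1.5, 1.5, 1.4, 1.2, 0.6 | item 6 at .30, others .48 | 9.26 | 28.27 | .807 |
| 1.0, 1.5, 1.5, 1.4, 1.2, 0.6 | item 6 at .20, others .53 | 9.26 | 29.21 | .820 |

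The third row falls below .80 while standardized alpha passes. In the last row the order reverses and raw alpha is the higher.

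A wider check drew 40,000 random one-factor patterns (loadings .4 to .9) for each of three SD ranges:

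| Item SD range | Mean gap (standardized minus raw) | 1st to 99th percentile | Patterns where the .80 verdict differs |
|---|---|---|---|
| 0.9–1.4 | .004 | −.005 to .017 | about 4% |
| 0.8–1.5 | .008 | −.005 to .029 | about 7% |
| 0.6–1.7 | .020 | −.004 to .061 | about 16% |

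**Alpha and dimension.** Take two clusters of three items with r = .70 within and .30 between. There are 6 within-cluster pairs and 9 between-cluster pairs.

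- Mean r = (6 × .70 + 9 × .30) / 15 = 6.9 / 15 = .46.
- Standardized alpha = 2.76 / 3.30 = .836, a pass.
- First two eigenvalues: 1 + 2 × .70 + 3 × .30 = 3.3, and 1 + 2 × .70 − 3 × .30 = 1.5. The other four are .3.
- Corrected item-total correlation: (2 × .70 + 3 × .30) / √14.2 = 2.3 / 3.768 = .61, above .40.

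With r = .80 and .20, alpha is .825, the eigenvalues are 3.2 and 2.0, and the item-total correlation is .59. In the limiting case of two uncorrelated, perfectly measured clusters (r = 1 and 0), alpha is exactly .80. Conversely, a true single factor with all r = .30 gives alpha 1.8 / 2.5 = .72 and fails.

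**The case against.** A reader might infer that the .80 mark says nothing about the reliability of the summed score. The documents do not support that. All items share a 1-to-5 range, so standardized alpha is a close approximation to raw alpha. The case that falls to .791 needs a mean correlation just above the threshold, SDs spanning 2.5-fold, and an item 6 with little spread that still correlates .42 with every other item. Letting that item correlate less brings raw alpha back above .80. The documents give no item SDs and show no bias in a known direction. The raw sum's stability is also covered by the test-retest ICC criterion of > 0.70.

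A reader might also infer that the study will report one dimension on alpha alone. That goes too far. The next sentence plans an exploratory factor analysis, and an oblique rotation has a role only if two or more factors are extracted. In the two-cluster example, a common eigenvalue-above-1 rule would retain two. The phrase about one dimension is an explanatory gloss, not a decision rule. The absence of a stated factor-retention rule is not counted here, because an article commonly leaves that to the full protocol or analysis plan.

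What remains is narrower. The named coefficient is not that of the score in use. The gloss gives alpha a meaning it does not have. And the two numeric marks in those sentences, alpha and item-total correlation, can both be met by two-factor data.

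**Conclusion.** The point holds as a minor one. Standardized alpha should be raw alpha for a score formed as a raw sum. The expected difference is about .00 to .03, of either sign, and is larger only when item SDs are very unequal. It would alter the pass or fail result mainly for values close to .80. The statement that alpha cannot establish one dimension does not depend on the size of that difference: with six items, alpha .836 is compatible with eigenvalues of 3.3 and 1.5. All SDs and correlations used are assumptions; with equal SDs the two alphas coincide.

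**What to change.** In Data analyses, Reliability:

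1. Replace standardized alpha with alpha computed on the raw item scores, reported with a 95% CI, and apply the > .80 mark to it.
2. Delete the wording that equates internal consistency, as measured by alpha, with one underlying dimension.
3. State that any claim of one dimension rests on the number of factors found in the exploratory factor analysis already planned. If more than one factor is retained, do not present the single alpha as evidence of one dimension.

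The cost is a change of wording and analysis code, with no new data. The reported coefficient may be slightly less favourable.
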